### Group allocation

For the standard cardiac rehabilitation group, participants will be consecutively recruited prior to commencement of outpatient cardiac rehabilitation. Patients who are eligible for but not participating in cardiac rehabilitation will be randomly allocated to either their modular or conventional care group immediately following completion of the baseline assessment. Therefore, the researcher conducting each baseline assessment will be blinded to group allocation. Prior to study commencement, a computer-generated allocation sequence will be constructed using randomly permutated blocks [25]. An individual not involved in the study recruitment, data collection or analysis will produce consecutively numbered sealed opaque envelopes containing each participant's allocation. Following baseline assessment, the researcher will select the next consecutively numbered envelope and open it to reveal the allocated group. They will then notate the unique patient identifier on the front on the participants cover sheet. Therefore, group allocation will be concealed from the researcher conducting baseline assessments.

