### Outcome measures

Assessments will be conducted in the hospital consulting rooms or in the participant's home, if they are unable to travel to the hospital. Demographic, subjective and objective information will be obtained during face-to-face assessments at baseline, three and 12 months. Information will include past history, nature of ACS, family history, age, medications and dose, presence of other cardiovascular disease and the nature and date of any revascularisation. In addition, contact details for each participant, their general practitioner and their cardiologist will be documented.

At three and 12 month follow-up, all baseline measures will be repeated during face-to-face assessments by a researcher blinded to group allocation. Additional collected information will include – details of unplanned hospital admissions, medications and doses along with details of any health interventions undertaken by the participant pertaining to their heart health, such as visits to the GP and attendance at community programs. For participants in the standard rehabilitation group, details of participation in the cardiac rehabilitation program will also be recorded such as duration and attendance at exercise and education sessions.

Modifiable risk factors to be measured are serum cholesterol, BP, smoking status, physical activity, overweight and depression. Lipids and substrates will be measured on a fasting blood sample within two weeks of assessment date. Participants will be referred to local pathology clinics by their primary care doctor and will visit the clinics by their own arrangement. Blood samples will be analysed for determination of total cholesterol (TC), low density lipoprotein cholesterol (LDL-C), high density lipoprotein cholesterol (HDL-C) and triglycerides (TG). Repeat blood tests will be carried out at the same pathology clinic wherever possible.

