### Procedure

#### Conventional care group

Participants randomly allocated to the conventional care group will continue to manage their heart health as directed by their primary care doctor or by their own cognisance. This group will not receive any additional intervention as a result of participation in the study. However, they will be contacted by telephone 2–3 weeks after baseline assessment to confirm their three month assessment appointment. In addition, each participant's general practitioner (GP) and cardiologist will be mailed a courtesy letter following baseline assessment and a risk factor summary with recommendations for discussion regarding long-term risk factor management following the final 12 month assessment.

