#### Modular group

Participants randomly allocated to the modular group will manage their heart health by participation in modular guided self-choice management of heart disease. That is, participants will participate in risk factor modules of their choice, with the exception of the mandatory blood cholesterol module, strive to achieve mutually-agreed goals and make choices about risk factor reduction interventions based on their own circumstances. Following baseline assessment, the consultation will be extended by approximately 30 minutes for selection of modules, goal setting and shared decision making about risk factor interventions.

The risk factor modules consist of cholesterol-lowering, BP management, smoking cessation and physical activity. All participants will participate in the cholesterol-lowering module and where applicable, participants can also choose up to two other modules depending on their individual risk factor assessment and personal preference. Therefore, all participants will participate in a minimum of one risk factor module and a maximum of three modules at any one time.

The mandatory cholesterol-lowering module involves pharmacological intervention in consultation with the primary care doctor as well as education and empowerment through information and support about individual and nationally recommended cholesterol levels. The three optional modules involve choice of intervention including; following medical advice; participating in a structured program (individual or group); participating in a home program; or self-help. All risk factor modules will be resourced and delivered separately among the primary care doctor, the local area health service, the local community and the participant. Participants in the modular group will receive a resource package including appropriate information leaflets which contain guidelines and information about the module and contact information for community heart health programs. The leaflets have been developed and pilot tested, for validity, by health professionals and consumers.

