For each risk factor module, a three month objective goal will be set based on shared decision-making. The mutually-agreed goal will be based on the each participant's risk factor profile, social factors, commitments and personal preference. Participants will also asked to rate their confidence in achieving the set goal on a visual analogue scale from 1–10. Each risk factor baseline level, mutually agreed goal, time frame and confidence rating will be recorded on the information leaflet.

All participants in the modular group will also be "coached" using a previously published model [38]. The coaching model is a five stage cyclic process and involves assessing understanding, providing education, assertiveness training and reassessment. In this study, the first coaching session will be conducted during the initial face-to-face shared decision making, goal setting session. Participants will then be coached over the telephone on up to four further occasions, depending on goal achievement, during the following three months depending on need. Once each risk factor goal is achieved, no further coaching is required. All coaching will be conducted by a researcher who has been trained by the original coach study coordinator. During each coaching session individual's knowledge of their risk factors and personal goals will be identified and participation in the module will be established and recorded.

Communication between the study coordinator, the participant and health professionals involved and community services will be facilitated where possible. Each participant will also be encouraged to communicate openly about their goals and modules with their local doctor and cardiologist. During the course of the study, participants identified as being clinically depressed, according to their CDS, are to be offered an appointment with a clinical psychologist specialising in heart disease. For each participant, their GP and cardiologist will be sent a comprehensive letter outlining the participant's risk factors, goals and chosen modules. Following the final 12 month assessment, all participants and their doctors will also receive a cardiac risk factor summary and recommendations for discussion regarding long term risk factor management. By facilitating communication, it is anticipated that each participant receives a coordinated multidisciplinary approach to their own risk factor management based on need and situation.

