### Sample size

Participant numbers required for each group have been calculated to detect a 0.5 mmol/L reduction in TC with 80% power. The LIPID study of 9014 subjects with CHD reported a mean TC of 5.6 (± 0.7) mmol/L [40] and it has been assumed that a clinically significant change in TC would be 0.5 mmol/L. Therefore, to achieve power of 80% to detect a change of 0.5 of a SD unit, using a two-tailed test with an alpha level of 0.05 and allow for 10% loss to follow-up, it was calculated that 72 participants per group will be recruited.

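### Total cholesterol, which sizes the trial, is obtained through the GP and a self-arranged clinic visit, a route the modular intervention reinforces, so missing values may differ by arm

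*Protocol article*

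**What the plan says.** The Sample size section of the Protocol article bases the trial on a 0.5 mmol/L reduction in TC. Serum cholesterol is also one of the modifiable risk factors listed under Outcome measures, and the Discussion names those risk factors as the primary outcomes.

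Outcome measures sets the route for the blood test. On timing: "Lipids and substrates will be measured on a fasting blood sample within two weeks of assessment date". On access: "Participants will be referred to local pathology clinics by their primary care doctor and will visit the clinics by their own arrangement". Repeat tests are to use the same clinic where possible. The other measurements follow a different rule: "Assessments will be conducted in the hospital consulting rooms or in the participant's home, if they are unable to travel to the hospital".

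The Modular group section makes the cholesterol module mandatory and describes it as involving "pharmacological intervention in consultation with the primary care doctor". It adds a first coaching session, up to four telephone sessions over three months, a comprehensive letter to the GP and cardiologist, and this: "Each participant will also be encouraged to communicate openly about their goals and modules with their local doctor and cardiologist".

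The Conventional care group section provides management by the participant's own doctor or by the participant, a courtesy letter to the GP and cardiologist after baseline, and one call at 2–3 weeks to confirm the three-month appointment.

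**The concern.** Blood pressure, expired carbon monoxide, weight, height and the questionnaires are obtained when a participant is assessed, with a home visit as fallback. A TC value needs two further steps: a referral from the GP and a clinic visit that the participant arranges. No home or study-run fallback is described for blood.

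The modular intervention encourages contact with the GP about cholesterol, so the path to measuring this outcome overlaps with the treatment under test. Participants in the two arms may complete it at different rates, and those who complete it may be the more engaged ones.

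The randomised population makes this plausible. It consists of people who have not attended rehabilitation, including some who refused or failed to attend. The Background attributes low participation to transport, work and social commitments, and lack of perceived need. Similar barriers could apply to a fasting test repeated at three time points.

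At stake is the TC contrast. The intention-to-treat analysis under Data analysis keeps participants in their allocated arm but does not supply a result that was never obtained. A missing TC also carries further: TC above 4.0 mmol/L is one item in each participant's count of modifiable risk factors, and that count is the yardstick for the knowledge question.

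**Working it through.** **The plan's own figure.** Inputs from Sample size: 0.5 SD, 80% power, two-sided alpha 0.05, 10% loss. A two-sample t-test needs 63.8, so 64 per group; 64 / 0.9 = 71.1, so 72. The stated 72 is reproduced. A change in the collection route leaves it unchanged.

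**Contact that could prompt a blood test, by arm.**
- Referral route: the same in all groups.
- Letter to the doctors after baseline: comprehensive (risk factors, goals, modules) in the modular arm; a courtesy letter in conventional care.
- Cholesterol module involving the GP: mandatory in the modular arm; none in conventional care.
- Telephone contact in the first three months: up to four coaching calls against one appointment call.
- Encouragement to talk to the doctor about goals: modular arm only.

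The arms therefore differ in intensity of prompting, although the nominal route is common to them.

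**Bias in a comparison of observed values.** Let m be the share of an arm without a TC value, and g the mean TC of untested minus tested participants in the same arm, with g equal in both arms. The full-arm mean is the tested mean plus m × g, so the tested mean is the full-arm mean minus m × g. Then

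bias in (modular − conventional) = (m_conventional − m_modular) × g.

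The document gives neither m by arm nor g. All values below are assumptions.
- 10% vs 25% missing, g = 0.3 mmol/L: (0.25 − 0.10) × 0.3 = 0.045 mmol/L, or 0.045 / 0.5 = 9% of the target.
- 10% vs 40% missing, g = 0.5 mmol/L: (0.40 − 0.10) × 0.5 = 0.15 mmol/L, or 0.15 / 0.5 = 30% of the target.
- 10% vs 20% missing, g = 0.2 to 0.7 mmol/L: 0.02 to 0.07 mmol/L.
- 10% vs 30% missing, g = 0.2 to 0.7 mmol/L: 0.04 to 0.14 mmol/L.
- Equal missing shares with the same g: zero.

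**Direction.** The modular benefit is a negative difference. With g positive (untested participants have higher TC) and more missing in conventional care, the bias is positive and the benefit looks smaller. If GPs more readily test patients with high cholesterol, g is negative and the benefit looks larger by the same amount.

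**The case against.** The strongest reply is that the article gives one referral route for everyone, does not say that a GP visit is needed for each referral, and gives no missing TC by arm. Conventional participants also have a GP, their doctors also receive a letter, and they too get a call. How forms are issued is detail that an article may leave to the full protocol. All of this stands. It limits the point to what may happen, but it does not remove the difference in prompting, which the article itself sets out.

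Four stronger readings are tempting and are not supported.
- *TC will be available unequally, and the tested controls will be a better-managed subset.* This is a prediction; the document supports neither the certainty nor the sign.
- *The trial loses material power.* With 65 and 54 evaluable, power at 0.5 SD is about 77%, against 81% with 65 and 65. That fall is small. At the stated 0.5 mmol/L with SD 0.7 (0.5 / 0.7 = 0.71 SD), power with 65 and 54 is about 97%. Power is not the argument.
- *The blood test contradicts the conventional-care promise that* "This group will not receive any additional intervention as a result of participation in the study". Outcome measurement is not an intervention, and it is the same in every group. That it generates a GP visit, or that the GP acts on the result, is inference.
- *The loss allowance covers missed visits only.* The text says just "allow for 10% loss to follow-up", which does not exclude missing blood results.

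TC is also one of several primary risk factors, and the others do not use this route.

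**Conclusion.** The point holds as a risk created by a stated design choice. The outcome that sizes the trial is collected by a route that depends on the GP and on the participant's initiative, and only one arm has an intervention that encourages GP contact about cholesterol. Missing TC may differ by arm and be related to engagement.

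No size or direction can be derived from the document. The illustrations of 0.045 and 0.15 mmol/L rest wholly on assumed missing shares, an assumed TC difference that is equal in both arms, and a comparison of observed values without adjustment. This is a cheap improvement to make before recruitment, because samples not taken cannot be recovered later.

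**What to change.** In Outcome measures, replace the referral that each participant obtains from the primary care doctor with a pathology request that the study prepares for every participant in all three groups, sent to the GP by post for signature beforehand. Hand it over at the baseline, three-month and 12-month assessments, and have the result copied to the study. Give the same fasting-test reminder in every group, outside the coaching calls, so that prompting to be tested is not part of the intervention. Report TC availability by arm at each time point.

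The cost is a little clerical work and postage. The sample size is unaffected.

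This change does not settle a separate matter of order. Participants are "randomly allocated to either their modular or conventional care group immediately following completion of the baseline assessment", so a baseline sample taken after that assessment also follows allocation.

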## Methods/Design

### Design

This randomised controlled trial with one year follow-up will be conducted at a tertiary referral hospital in Sydney, Australia. Participants not attending standard cardiac rehabilitation will be randomly allocated to either a modular secondary prevention (experimental) or a conventional care (control) group. A third contemporary group of patients attending standard cardiac rehabilitation will also be recruited (reference group). Ethical approval for the study has been granted by both the Central Sydney Area Health Service CRGH Zone and the University of Sydney Human Research Ethics Committees. Written and informed consent will be obtained from all participants prior to commencement.

Independent variables are the identification of individualised risk factor goals and participation in self chosen secondary prevention modules. The dependent variables are assessment of cardiac risk factors, the achievement of risk factor goals, unplanned hospital readmissions, quality of life, relative cardiac risk and knowledge of risk factors. The measurement and recording of experimental variables will be conducted under blind conditions.

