Relative cardiac risk will be calculated using the LIPID score which was developed for use in secondary prevention [37]. An individual's risk score calculation involves aggregating risk point estimates corresponding to the patient's risk factor profile. Aggregate scores provide an indication of the level of risk for a future ACS. The scores are divided as low risk (≤ 4), medium risk (5–6), high risk (7–9) and very high risk (≥ 10) [37]. Further, each participants number of modifiable risk factors will be calculated using the cut points; TC > 4.0 mmol/L, SBP ≥ 140 mmHg, current smoking, physical inactivity using the categorical IPAQ score, BMI ≥ 30 kg/m^2^, known diabetes and a CDS score ≥ 90 for depression.

Each participant's knowledge of their own cardiovascular risk factors will also be assessed at baseline, three and 12 months. Participants will be asked if they can state any of their own modifiable risk factors for heart disease and the number stated will be compared to the each individual's actual number of modifiable risk factors. Participants will then be asked if they are able to state the Australian recommended targets for total cholesterol, BP, physical activity and whether or not smoking is recommended for people with CHD.

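### Knowledge of own risk factors is scored by comparing counts rather than matched items, against a reference visit that is not fixed; goal achievement is defined only in the modular arm and can only be descriptive there

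*Protocol article*

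**What the plan says.** **Knowledge.** Under Outcome measures: "Each participant's knowledge of their own cardiovascular risk factors will also be assessed at baseline, three and 12 months". The scoring rule is that "the number stated will be compared to the each individual's actual number of modifiable risk factors". The paragraph before it builds that number from seven items: total cholesterol (TC) above 4.0 mmol/L, systolic pressure of 140 mmHg or more, current smoking, inactivity, BMI of 30 or more, known diabetes, and a depression score of 90 or more. The same section repeats all baseline measures at three and 12 months. A second knowledge item asks for the Australian recommended targets. The Discussion names knowledge as a secondary outcome.

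**Goals.** The Design section says "Independent variables are the identification of individualised risk factor goals and participation in self chosen secondary prevention modules", and then "The dependent variables are assessment of cardiac risk factors, the achievement of risk factor goals" with further outcomes. Goal setting is described only under Modular group: "For each risk factor module, a three month objective goal will be set based on shared decision-making", and "The mutually-agreed goal will be based on the each participant's risk factor profile, social factors, commitments and personal preference". For conventional care the article says "This group will not receive any additional intervention as a result of participation in the study". The Discussion does not list goal achievement as primary or secondary.

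**Analysis.** Data analysis plans comparisons of outcome measures between and within groups, in general terms.

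**The concern.** Knowledge is part of the stated objective, so its score should respond to what a participant knows and to nothing else. The stated rule can fail in two ways.

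- A wrongly named factor can make up for a missed one, because only the totals are compared.
- The total compared against may itself respond to treatment. Four of the seven counted factors (cholesterol, blood pressure, smoking, physical activity) are the subjects of the modules. If the reference is the count at each visit and the intervention works, the reference shrinks more in the modular arm, and a benefit already counted under risk factors could be reported again under knowledge.

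For goal achievement, the treatment supplies the outcome's reference value. The goals are negotiated one by one and have no described counterpart in conventional care.

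**Working it through.** **No figure to reproduce.** The article gives no number for either outcome. Its only planning figure, 72 per group, rests on TC. A two-sample t-test at 0.5 SD, 80% power and two-sided 0.05 needs 64 per group, and 64/0.9 = 71.1, rounded up to 72. I use 64 per arm below as the number expected to be analysed.

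**1. Counts against items.** Take a participant with high TC, high systolic pressure and inactivity who names smoking, overweight and diabetes. Number stated 3, actual number 3: full agreement. Matched items: 0 of 3 correct, with 3 wrong.

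**2. Moving reference.** Take a participant with four factors at baseline who names three of them correctly. Two factors later fall below their cut points and the same three are named.

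- As a ratio: 3/4 = 75% becomes 3/2 = 150%.
- As a signed difference: 3 − 4 = −1 becomes 3 − 2 = +1.
- As an absolute difference: 1 stays 1. Had three factors resolved, it would be |3 − 1| = 2, which is worse.

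Knowledge has not changed in any of these. The article says only that the numbers are compared, so both the size and the direction of the artefact depend on a score it does not define.

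**3. How large it might be (all inputs assumed).** Baseline prevalences: TC 0.70, systolic pressure 0.35, smoking 0.20, inactivity 0.45, BMI 0.35, diabetes 0.20, depression 0.20. Each baseline factor is named with probability 0.3 to 0.7, the same in both arms. Each of the four module factors resolves with probability 0.10 in conventional care and 0.20 to 0.50 in the modular arm.

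- Between-arm difference in mean (stated − current count) = (sum of the four prevalences) × (difference in resolution). The sum is 0.70 + 0.35 + 0.20 + 0.45 = 1.70. So 1.70 × 0.10 = 0.17 and 1.70 × 0.40 = 0.68 factors, in favour of the modular arm. Simulation agrees.
- Simulated share with stated at or above the current count: the arms differ by 5 to 26 percentage points. With 64 per arm, that would be declared significant in about 11% to 84% of trials.
- With equal resolution (0.10 in both arms), or with the baseline count as reference, the difference is nil apart from simulation noise.
- If items are matched but the current list is used, the share naming every current factor still differs by 3 to 14.5 points, because a shorter list is easier to complete.

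**4. Check on the cholesterol input.** The Sample size section gives mean 5.6 and SD 0.7 mmol/L. Assuming normality, the share at or below 4.0 is Φ((4.0 − 5.6)/0.7) = Φ(−2.29) ≈ 1%. After a 0.5 reduction it is Φ((4.0 − 5.1)/0.7) = Φ(−1.57) ≈ 6%. Cholesterol would then add only about 0.05 factors to the difference. The other three add 1.00 × 0.10 to 1.00 × 0.40, so the range becomes about 0.15 to 0.45. The upper end in step 3 is therefore too high on the article's own planning figures.

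**5. Goal achievement.** Design makes goal identification part of the treatment and goal achievement an outcome. Modular group sets one goal per module, for one to three modules at a time, by agreement. Conventional care has none described. No between-arm value can be formed, and within the modular arm there is no common standard.

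**The case against.** The strongest reply is that the article does not fix the readings on which the damage depends. It asks for the participant's own factors, so a reader may assume that only correct ones are counted. It does not say that the current visit supplies the reference, and with the baseline count the moving reference disappears. It defines no ratio, so 150% is a construction. If items had to be the participant's own at that visit, the proportion could not exceed 100%, and with equal recall per factor its expected value would not depend on how many remain. Detailed scoring may sit in the full protocol or analysis plan.

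Most of this stands, and it limits the claim about size. It does not remove the point about counts, because the rule that is stated compares numbers, and matching has to be read into it.

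A reader might go further and infer that neither outcome can be fairly compared between arms. The documents do not support that. The recommended-targets item has an external standard common to all groups. The reference visit is left open rather than wrongly fixed. Goal achievement is neither primary nor secondary in the Discussion, and nowhere is it explicitly compared between arms.

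A fixed baseline list also has a cost: it ignores factors that arise later and may penalise someone, such as an ex-smoker, who reasonably no longer names a resolved one.

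**Conclusion.** The point holds in limited form. As stated, the own-risk-factor score compares totals, so wrong answers can offset missed ones. If the actual number is taken at each visit, the same answers can score differently by arm whenever risk factors are better controlled in one arm, which is what the trial hopes to achieve. That second part is conditional on a reading the article neither states nor rules out. Its size is not derivable from the documents: the 0.17 to 0.68 factors and the 11% to 84% rest wholly on assumed prevalences, recall and resolution, and the upper end is doubtful for cholesterol. They show only that the artefact need not be trivial.

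The goal part is firm but minor: with goals described in one arm only, achievement can be reported there but cannot give a randomised comparison.

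**What to change.** - **Record** which factors each participant names at each visit, not only how many.
- **Score** item by item: the proportion of the participant's own factors correctly named, with wrongly named factors counted separately.
- **Reference:** use the baseline list as the fixed denominator at all visits for the between-arm comparison. Repeat with the current-visit list as a sensitivity analysis, which covers the baseline list's blind spot for new and resolved factors.
- **Goals:** label achievement of mutually agreed goals as a descriptive outcome of the modular arm. For any between-arm comparison of target attainment, use the common cut points already given under Outcome measures, adjusted for baseline.

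The cost is one scoring rule, one outcome label and possibly a line on the data form. No new measurement or visit is needed. It should be settled before data collection, because item scores cannot be recovered if only the totals were written down.
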